**Figure 2 figure2:**
[figure not shown]
Feature extraction and quantification of behaviors relevant to neuropsychiatric diagnostics. LSTM: Long Short-Term Memory network.

For complex social features beyond the scope of automated ML-powered computational processing, we will deploy a novel crowdsourcing framework consisting of a crowd worker profiling phase, followed by a study data tagging step. In the first phase, we will post 20 tasks on Amazon Mechanical Turk, each presenting a video acquired through pilot testing of the gamified social data collection platform, followed by a series of multiple-choice questions corresponding to items from the diagnostic criteria for ADHD and ASD, as defined by the DSM-5. Each task will correspond to a separate video, and there will be 4 videos per diagnostic category used to quantify worker abilities. Worker responses will be compared against the Clinical Global Impression gold standard ratings provided by our collaborators in the Department of Psychiatry at the University of Hawai‘i. Crowd workers who align with the ratings of clinical experts on at least 1 behavioral feature, where alignment is defined as <1 categorical ordinal deviation per 2 videos, will be recruited to label the final study data from 400 participants. Recruited workers will only label those features for which their alignment with clinicians was demonstrated during the profiling phase as shown in Figure 3.

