#### Evaluation

To assess the effectiveness of the crowdsourcing pipeline, we will compare the performance of crowd workers before and after their recruitment. The preliminary data show that crowd workers who answer similarly to clinicians during filtering continue to perform in a similar manner on new, unseen videos. We will also measure crowdsourcing metrics such as latency to starting a task, interrater reliability, any decline in performance with increased ratings, and the completion rate for all assigned tasks. To evaluate the privacy-preserving mechanisms, we will randomly assign each worker to a single privacy condition per video, only asking them to rate the unaltered videos after the ratings for the privacy condition have been provided. We will measure the mean deviation from clinician answers per privacy condition for each question.

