### Novel Crowd-Powered and Traditional ML-Based Feature Extraction

We have conducted a series of preliminary studies testing the use of crowdsourcing for precision behavioral health, demonstrating that although there is a high degree of variability in crowd workers’ innate ability to rate complex social behaviors in unstructured home videos [10], there exists a small fraction of crowd workers on platforms such as Amazon Mechanical Turk who consistently rate in alignment with licensed clinical experts [48,49]. In a study, we demonstrated that a group of 40 crowd workers filtered from an original pool of >1000 workers was able to rate behaviors that, when fed into a classifier trained on clinician records, achieved an AUROC of 0.9904 for one set of features and 0.9872 for another feature set [42]. Our experience of receiving approval from university IRBs and data privacy offices as well as obtaining consent from families to share their videos with crowd workers mitigates any risks related to this novel process.

After applying privacy-preserving modifications to the videos, such as pitch shifting the audio downward and using face detection to box out the child’s face, the performance of the model remained >0.95 for both AUROC and area under the precision-recall curve [42]. Although these results show promise for predicting autism in a binary task, they are likely to decline in accuracy when expanding to include ADHD as a diagnosis too. These studies provide strong evidence to support the proposed worker matching procedure, which will enable the more nuanced feature space required for multicondition classification. The prior experience in developing automated pipelines for managing crowd workers will help streamline the development of the crowd management scripts.

The feasibility of the automatic feature extraction steps comes from the existing packaging of the required functionalities into Python libraries and the high documented performance of these tools. All the ML-powered feature extractors we have used are well documented.

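### The worker filter has no base-rate correction, so a constant rater can qualify on skewed items, and the before-after comparison appears to reuse the score on which workers were selected

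*Protocol article*

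**What the plan says.** All references are to the protocol article.

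- **Profiling (Feature Extraction, Description).** "In the first phase, we will post 20 tasks on Amazon Mechanical Turk", each with its own video, and "there will be 4 videos per diagnostic category used to quantify worker abilities". Workers answer multiple-choice questions on DSM-5 items and are compared with clinicians' ratings.
- **Gate.** "Crowd workers who align with the ratings of clinical experts on at least 1 behavioral feature" are recruited, where "alignment is defined as <1 categorical ordinal deviation per 2 videos".
- **Restriction.** "Recruited workers will only label those features for which their alignment with clinicians was demonstrated during the profiling phase".
- **Evaluation of the pipeline (Feature Extraction, Evaluation).** "we will compare the performance of crowd workers before and after their recruitment". The section adds, without a figure, that preliminary data show "crowd workers who answer similarly to clinicians during filtering continue to perform in a similar manner on new, unseen videos".
- **Use of the ratings (Multicondition Diagnostics, Description).** The plain mean of crowd responses is the baseline quantification of each behavior. A model that also uses worker metrics is to be explored.
- **Fallback (Limitations).** A question is removed if no worker rates it consistently with clinicians.

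The number of answer levels per item and the distribution of clinician ratings are not given.

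**The concern.** The gate counts raw disagreement. It does not ask whether the worker can tell a video that shows the behavior from one that does not. If clinicians give most videos the same rating, repeating that rating keeps the deviation low. By Table 1 several behaviors belong to one condition only, and Related Work notes that not every defining symptom need be present, so skewed items are to be expected. A constant rater contributes nothing to the mean crowd rating except dilution. Such raters can also keep a question in the study that the Limitations fallback would otherwise remove.

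The second problem is the yardstick. Workers are recruited because their deviation on the profiling videos was low. If that same deviation is the before value, it is too favorable in expectation, and the later value will tend to look worse even when ability has not changed. The comparison meant to show whether the pipeline works would then mix selection with performance. The Methods overview makes the adaptive querying and the differential diagnosis depend on crowdsourcing, so both points touch the core of the design.

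**Working it through.** The article states no pass rate or error rate for the filter, so there is no figure to reproduce first.

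**Threshold.** Fewer than 1 step per 2 videos, over 20 videos, means a total below 20/2 = 10. That is at most 9 steps, or a mean below 0.5 per video.

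**Constant rater, yes/no item.** Take a behavior that Table 1 gives to ASD only. Suppose all ASD-only and all comorbid videos show it and no others do: 4 + 4 = 8 of 20. Always answering absent gives 8/20 = 0.40 < 0.5, a certain pass. (Four videos for each of the four named outcomes would give 16, not 20. Then 8/16 = 0.50 just fails, and 7/16 = 0.44 passes once one such video lacks the symptom.) If each video is instead positive independently with probability 0.4, P(Binomial(20, 0.4) ≤ 9) = 0.76. At probability 0.2 it is 0.997.

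**Constant rater, ordinal item.** The answer levels and clinician distributions here are assumptions. The per-video deviation of the best constant answer was convolved exactly over 20 videos to give P(total ≤ 9). For three levels at 60/25/15 the expected deviation is 0.25 + 2 × 0.15 = 0.55. At 80/12/8 it is 0.12 + 2 × 0.08 = 0.28.

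| Levels | Clinician ratings evenly spread | 60% lowest | 80% lowest | Uniform guesser |
|---|---|---|---|---|
| 3 | 4% | 34% | 92% | 0.2–0.5% |
| 4 | 0.03% | 17% | 79% | <0.01% |
| 5 | <0.001% | 11% | 73% | about 0.0001% or less |

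The first three result columns are for the constant rater. The chance lies in which clinician ratings the profiling set happens to contain. On a given item, therefore, all workers who repeat that answer pass or fail together.

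**Before and after.** Assume each worker has a stable true deviation rate, scores 0 or 1 per video, is selected at a mean below 0.5 on 20 videos, and then rates 20 new videos. The distribution of true rates is an assumption.

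| True rates | Share passing | Before (selected) | After (selected) | Apparent decline |
|---|---|---|---|---|
| two clean groups, 0.1 (4%) and 0.9 | 4% | 0.100 | 0.100 | about 0 |
| beta(2,4) | 76% | 0.242 | 0.263 | 0.02 |
| beta(2,2) | 47% | 0.280 | 0.317 | 0.04 |
| beta(5,5) | 45% | 0.333 | 0.389 | 0.06 |
| beta(20,20) | 43% | 0.374 | 0.458 | 0.08 |
| beta(20,10) | 8% | 0.406 | 0.562 | 0.16 |

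Ability is unchanged in every row. If before covers all profiled workers, beta(2,2) gives 0.499 before and 0.317 after, an apparent improvement produced by selection alone.

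**The case against.** **Item type.** Multiple-choice questions and ordinal deviations suggest more than two levels. The yes/no figures may then not apply, and a constant rater on an evenly spread item rarely passes. This stands. A reader might infer that uninformative raters qualify in general, because a coin-flipper passes a yes/no item with probability 0.41 and so passes at least one of ten independent items with probability 1 − (1 − 0.41)^10 = 0.995. The documents do not support that inference. They do not say the items are yes/no, and a worker labels only the features passed, so passing one item opens no other.

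**Strict reading of the threshold.** If no deviation at all were allowed in any pair of videos, chance passing would be negligible (0.5^20, about 1 in a million, for a yes/no guesser). The wording reads more naturally as a rate.

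**Prior experience.** The Results describe "a group of 40 crowd workers filtered from an original pool of >1000 workers", and preliminary data are said to show stability on new videos. Both suggest that good workers may stand out clearly, which is the low-artefact case. But the earlier study is not said to have used this rule, and the stability claim has no figure.

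**Later safeguards.** Interrater reliability, decline over ratings, worker-variability metrics and recurring gold questions could expose constant raters. They soften the harm. None gates recruitment, constant raters agree with one another, the payment bonus also rewards raw agreement, and the baseline remains the plain mean.

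**Direction of the bias.** A reader might infer that a decline is built in. It is not: the decline holds only in expectation and only for recruited workers, it can be close to zero, and it reverses if before means everyone profiled. The Evaluation section does not say which is meant.

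**Conclusion.** The point holds in a limited form. The gate as written lets a constant rater qualify on items where clinician ratings are skewed: with certainty on a yes/no item present in 8 of 20 videos, and with probability of about 34% to 92% on a three-level item with 60% to 80% of ratings lowest. These figures rest on the rate reading of the threshold and on assumed levels and distributions. They do not extend to uniform guessers on items with three or more levels.

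The before-after comparison, with the selection score as its only described baseline, carries an expected shift of about 0 to 0.16 deviations per video for recruited workers of stable ability, depending on how worker ability is distributed. With all profiled workers as the baseline the error runs toward improvement. On either reading the comparison does not isolate performance after recruitment unless workers separate cleanly. This is worth correcting because the correction is cheap. It does not show that the crowd features will fail.

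**What to change.** 1. **Gate (Feature Extraction, Description).** Add that a worker qualifies on a feature only if the present threshold is met and the worker's deviation is also below that of the best constant answer for that feature on the profiling videos. A constant rater then cannot pass, because the best that worker can do is equal the benchmark. Where clinician ratings are evenly spread, the present threshold will usually remain the binding one.
2. **Comparison (Feature Extraction, Evaluation).** State that it concerns recruited workers, and take the before score from ratings not used to select them. One way is leave-one-video-out: score each profiling video over all workers who meet the full rule on the other 19, including any whose answer on the held-out video would have cost them their place. Dropping those workers would bring the bias back. Compare the result with clinician-rated gold questions answered after recruitment, which the Limitations section already plans. This nearly removes the expected shift; a small remainder comes from applying the rule to 19 videos instead of 20.

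Cost: a changed scoring rule on tasks already planned, with no new videos. Fewer workers will qualify for rarely seen behaviors, and a behavior that clinicians rate identically in every profiling video will have none. The Limitations section already says what happens to a question with no qualifying worker.

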**Figure 3 figure3:**
[figure not shown]
Crowd worker assignment to labeling tasks. Each crowd worker will only be asked to label those features for which they agreed with clinicians during a worker profiling step performed before the primary study.

A valuable by-product of this process will be the generation of large behavioral multimedia data sets for ML of complex social features, enabling improved artificial intelligence modeling of human behavior more broadly. With explicit permission from study participants on a per-video basis, we will package and publish the collected data into novel computer vision, audio, and natural language processing data sets for ML. These labeled data sets will be released publicly, providing a stepping stone toward improved automated methods for quantifying complex human behavior.

#### Evaluation

To assess the effectiveness of the crowdsourcing pipeline, we will compare the performance of crowd workers before and after their recruitment. The preliminary data show that crowd workers who answer similarly to clinicians during filtering continue to perform in a similar manner on new, unseen videos. We will also measure crowdsourcing metrics such as latency to starting a task, interrater reliability, any decline in performance with increased ratings, and the completion rate for all assigned tasks. To evaluate the privacy-preserving mechanisms, we will randomly assign each worker to a single privacy condition per video, only asking them to rate the unaltered videos after the ratings for the privacy condition have been provided. We will measure the mean deviation from clinician answers per privacy condition for each question.

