### Ethical Considerations

This study has been approved by the University of Hawaii Institutional Review Board (IRB; 2022-00909). We will only collect data from voluntary participants who sign an informed consent (parents) and assent (children) document during the intake session of the study. Participants whose videos will be shared for the 20 crowdsourcing tasks used to filter workers will be contacted by the study team to have a thorough discussion about the planned use of those videos. Workers who are qualified to rate the remaining videos for ≥1 question will be required to complete The Health Insurance Portability and Accountability Act training and The Collaborative Institutional Training Initiative training and will be required to encrypt their laptops using whole disk encryption. These workers will be added to the IRB protocol and will become official members of the study team after thorough training.

Although we will require participants to consent to sharing videos with crowd workers who have undergone thorough training, the clinical translation of this diagnostic system will require a more scalable approach that is sensitive to privacy concerns. We will experiment with privacy-preserving alterations to the curated videos to obfuscate identifiable information from the videos without degrading the feature-tagging performance of workers. Examples include pitch shifting the audio, which will allow workers to understand the content of the speech, and pixelating the video, which will obscure the participant’s background and face but would still allow workers to observe body movement patterns. We will measure the extent to which each privacy-preserving mechanism degrades the answers to each question.

We will deidentify the participant data and anonymize any personally identifiable information. All the data will be immediately uploaded to our secure and encrypted server on Amazon Web Services (AWS) [50], which is Health Insurance Portability and Accountability Act–compliant. A fully anonymized version of the data set will be released to researchers only after signing a data use agreement, which will be approved by the University of Hawai‘I Data Governance Office.

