The other potential pitfalls are compliance and tardiness. We will run automated computer vision checks in real time to ensure participant compliance with camera calibration requirements. Another script will send automated text messages and email reminders to late participants, assigning them to makeup sessions. If these mitigation steps fail or if recruitment is unsuccessful and there are <100 participants with valid data per diagnostic category, the study can still be successful with as few as 20 participants per class, as ML studies with approximately 20 participants per diagnostic category have frequently been published in the field [47].

There are also limitations associated with crowdsourcing based on the expertise of the crowd workers or their temporal availability. Although this never occurred during preliminary data collection, a potential pitfall is that some questions may have no workers who consistently rate them in accordance with clinicians. If this occurs, then that question will be removed from any further components of the study (ie, removed as a feature for the diagnostic classifier).

In crowdsourcing, scaling the number of workers does not correlate with the time spent on recruitment. However, to ensure high-quality annotations, we do anticipate spending a considerable amount of time recruiting crowd workers. As mentioned previously, we plan a crowd worker profiling phase based on 20 tasks and data collected through pilot studies with our data-gathering platform. By periodically posing a gold-annotated question and providing a monetary bonus for correctly answering such questions, we incentivize workers to provide high-quality answers. On the basis of our prior studies, we expect that the level of compensation will lead to a worker retention rate of >90%. Furthermore, to account for the loss of workers, we will recruit 3 times more crowd workers than is minimally required for the study. With regard to the number of crowd workers required, we follow the study by Roitero et al [70]. As such, the recommended number of workers will be estimated based on a small amount of data collected during our pilot studies.

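### The loss of rating quality relative to unaltered video is fully confounded with rating order, because the unaltered version is always rated second

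*Protocol article*

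**What the plan says.** The aim is given under Ethical Considerations: "We will measure the extent to which each privacy-preserving mechanism degrades the answers to each question". More than one mechanism is planned: "Examples include pitch shifting the audio, which will allow workers to understand the content of the speech, and pixelating the video".

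The design is given in the Evaluation subsection of Novel Crowd-Powered and Traditional ML-Based Feature Extraction. On allocation: "we will randomly assign each worker to a single privacy condition per video". On order: "only asking them to rate the unaltered videos after the ratings for the privacy condition have been provided". On outcome: "We will measure the mean deviation from clinician answers per privacy condition for each question". The same subsection also plans to track "any decline in performance with increased ratings", but does not connect this with the privacy comparison.

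Neither section describes counterbalancing of the order, or a group of workers who rate the unaltered version first.

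**The concern.** Degradation is a difference: how much worse the answers are with the alteration than without it. The randomization covers only the choice among altered versions. The without-alteration rating always comes from a worker who has already watched the altered version and answered the same questions.

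That second rating differs from the first in more than the picture and sound:

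- The worker may repeat the first answer (anchoring), which shrinks the apparent degradation.
- The worker may do better for having seen the material twice, which inflates it.
- The worker may do worse through fatigue, which shrinks it.

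What is at stake is the interpretation of the privacy evaluation. Ethical Considerations presents the alterations as a step towards a more scalable, privacy-sensitive system for later clinical use. For that purpose one needs to know what each alteration costs compared with clear video, and this is the quantity that the fixed order biases.

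**Working it through.** The plan states no figure for this evaluation, so there is none to reproduce. Two checks apply.

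**1. Can the contrast be separated from order?**

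Inputs from the document: one randomly assigned altered version per worker and video; altered first, unaltered second. Assumed: K = 3 altered versions. The result does not depend on K.

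Write each rating's deviation from the clinician answer as an intercept, plus an indicator for each altered version (A1, A2, A3), plus an indicator S for a second rating. That is 5 columns. Under the fixed order, every first rating is altered and every second rating is unaltered, so in every row

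A1 + A2 + A3 + S = 1 = the intercept column.

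| Design | Columns | Rank | Altered minus unaltered | Altered version 1 minus 2 |
|---|---|---|---|---|
| As written | 5 | 4 | not estimable apart from order | estimable |
| Unaltered added as a randomized first-rating condition | 5 | 5 | estimable | estimable |
| Order randomized | 5 | 5 | estimable | estimable |

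The dependency is structural, so sample size does not remove it. The number of workers is in any case still open (Limitations: "the recommended number of workers will be estimated based on a small amount of data collected during our pilot studies").

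The aliasing concerns first against second exposure to the same video. The text does not exclude that a worker rates one video unaltered before rating another altered, so general practice or fatigue along the whole task sequence is not necessarily aliased.

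**2. Which way could the bias go?**

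Let U be the mean deviation on unaltered video at first exposure, D the true degradation, a the share of answers simply repeated, and p the gain from a second viewing (negative for fatigue). A larger deviation means a worse rating.

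- First rating, altered: U + D
- Second rating, unaltered: (1 − a)(U − p) + a(U + D)
- Observed degradation, first minus second: (1 − a)(D + p)

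U cancels. Repeated answers show no second-viewing gain either, so a attenuates p as well as D. All values below are assumptions; the document supplies none. With D = 0.30 categories:

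| a | p | Observed degradation |
|---|---|---|
| 0 | 0 | 0.30 |
| 0 | 0.10 | 0.40 |
| 0 | 0.20 | 0.50 |
| 0 | −0.10 | 0.20 |
| 0.5 | 0 | 0.5 × 0.30 = 0.15 |
| 0.5 | 0.10 | 0.5 × 0.40 = 0.20 |
| 1 | any | 0.00 |

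The same true effect can thus look absent or be overstated by two thirds (0.50 / 0.30 = 1.67).

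**The case against.** The strongest defence is that the stated outcome is deviation from clinicians, an external reference, and not the worker's change between ratings. Every altered rating is a first exposure, uninformed by the clear video, which is a good reason for putting the altered version first. Two quantities are therefore free of order effects: absolute accuracy under each alteration, and the randomized comparison between alterations. This stands. A reader might infer that the privacy effect cannot be estimated at all, and the document does not support that.

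Nor does it support the inference that a harmful alteration would pass unnoticed. Anchoring acts only on the second, unaltered rating. Poor accuracy in the altered rating would still show against the clinicians.

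The defence does not cover the aim itself. Absolute error under an alteration does not say how much of that error the alteration caused, since workers also err on clear video: the Results section reports wide variation in their ability. Ranking the alterations does not show whether even the best one costs little. Ratings from the worker profiling phase are no clean baseline either, because they come from different pilot videos and workers are selected on them.

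The article does not say how long after the altered rating the unaltered one follows, and a condensed article may leave this out. A gap would weaken memory effects, but the order would still be fixed.

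**Conclusion.** The point holds for one contrast. Degradation relative to unaltered video, which is the aim stated under Ethical Considerations, is completely confounded with first-versus-second rating of the same material, and the direction of the bias is unknown. This follows from the stated order and the absence of any described counterbalancing; it needs no assumption about effect sizes. The size of the bias cannot be given from the document, and the 0.00 to 0.50 range around a true 0.30 is illustration only.

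Deviation from clinician answers under each privacy condition and comparisons between privacy conditions are unaffected. It would also be wrong to carry the point over to the diagnostic classifier: its evaluation is planned separately under Multicondition Diagnostics With Adaptive Input Querying, and nothing here invalidates it.

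The change should be made before tagging begins, because a worker who has rated the altered version of a video can no longer give a first-exposure rating of the unaltered one.

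**What to change.** - Make unaltered video one of the randomized first-exposure conditions for each worker-video pair.
- Rotate conditions over videos within worker, so that worker and video differences can be removed.
- Base the degradation contrast on first-exposure ratings only, in a model with worker and video effects (for example, crossed random effects), for each question.
- Drop the second, unaltered rating, or keep it as descriptive only.

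Cost: a change to task assignment, with no additional participants. If second ratings are dropped, fewer ratings are paid for per worker-video pair. There are two small downsides. The altered-versus-unaltered comparison is no longer the same worker on the same clip, and some first-exposure ratings go to the unaltered condition, leaving fewer for each alteration.
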